### Measurements

We will collect clinical data at scheduled timepoints throughout the study, with assessment frequency reflecting each measure’s expected rate of change and the need to balance data collection with participant burden. The daily-life data from the TOLIFE Kit will be collected continuously during the study (figure 1).

#### Clinical outcomes

We will collect data on moderate (requiring treatment with short-acting bronchodilators and oral corticosteroids, with or without antibiotics) and severe (requiring hospitalisation or an emergency room visit) exacerbations from medical records at each study visit, using the Global Initiative for Chronic Obstructive Lung Disease (GOLD) guidelines to define severity.^1^ For each exacerbation, we will additionally record the start and end dates of treatment, emergency room visits, hospital, home or intensive care unit admissions, the need for mechanical ventilation and any exacerbation-related deaths.

We will assess HRQoL using the validated German, Italian and Spanish translations of the COPD Assessment Test (CAT)^19^ and the Clinical COPD Questionnaire (CCQ)^20^ at every study visit. The CAT score ranges from 0 to 40, with higher scores (>10) indicating a more severe impact of COPD on a patient’s life. The CCQ is scored in three subdomains (symptoms, functional state and mental state) and a total score, all of them ranging from 0 to 6, with higher scores indicating worse health status.

We will assess dyspnoea severity using the modified Medical Research Council (mMRC) Dyspnoea Scale at every visit,^21^ which measures the level of breathlessness on a scale from 0 (breathlessness with strenuous exercise) to 4 (breathlessness with minimal effort).

We will assess functional exercise capacity using the 6-minute walk test (6MWT) according to ERS/ATS guidelines^22^ at visits T1, T3 and T5 (figure 1). The 6MWT is a self-paced walking test in which participants walk as far as possible in 6 min along a flat corridor, with a length of 30 m at Azienda Ospedaliero Universitaria Pisana and Hospital del Mar, and 20 m at the Pulmonary Research Institute. Before and after the test, we will measure oxygen saturation, heart rate, blood pressure and the Borg dyspnoea and fatigue scores. During the test, we will record the number of breaks and their duration. After the test, we will monitor recovery by measuring oxygen saturation and heart rate every minute for 5 min, and calculate the 6-minute walk distance (6MWD).

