**Methods and analyses:**

TOLIFE CSA is a longitudinal observational study that will recruit 150 clinically stable people with COPD from three clinical sites in Spain, Italy and Germany. Over 1 year, participants will attend quarterly in-person visits to collect clinical data, while being continuously monitored using six unobtrusive smart sensing devices collecting daily metrics calculated from triaxial acceleration, angular velocity, photoplethysmogram, sound intensity, changes in latitude and longitude, ambient light intensity, biomechanical pressure and respiratory airflow parameters. Clinical outcomes are exacerbation onset through medical records; 3-month changes in HRQoL through the COPD Assessment Test and the Clinical COPD Questionnaire; 3-month changes in dyspnoea severity through the modified Medical Research Council Dyspnoea Scale; and 6-month changes in functional exercise capacity through the 6-minute walk test. We will train, internally validate and test AI-based models (Random Forests, XGBoost, multilayer perceptrons, cumulative link model and standard classification model) to predict clinical outcomes.

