### Statistical analysis

The characteristics of the participants will be summarised using means and SD for continuous variables and frequencies and percentages for categorical variables.

The collected data will be processed through a modular modelling architecture. Low-level models will convert raw sensor outputs from each device (continuous physiological signals, discrete events and questionnaire-derived outcomes) into standardised physiological and behavioural indicators. These indicators, integrated with clinical variables, will serve as inputs to the higher level predictive models.

To predict the onset of moderate-to-severe COPD exacerbations, both rule-based and machine learning approaches will be compared during development, with the single best performing strategy in terms of predictive accuracy and clinical interpretability selected for the final system. The model will output a continuous daily probability score estimating exacerbation risk within a given future time window, rather than a binary prediction. To predict changes in 6MWD, CAT, CCQ and mMRC outcomes, we will model their levels and their changes over time, both as continuous and dichotomised according to minimal importance difference (following the most recent literature cut-offs at the time of data analysis), using a cumulative link model or a standard classification model, respectively. Predictors will consist of sensor-derived indicators, aggregated over different temporal windows (eg, 7, 14, 21 and 30 days for the exacerbation models; 21-day summaries for the 6MWD, CAT, CCQ and mMRC models), together with clinical variables.

For all models, statistical inference will rely on a clustered bootstrap approach with resampling at the participant level to account for repeated measurements; a group-based validation strategy will be adopted, with training and testing sets separated at the clinical centre level to prevent information leakage and assess cross-site generalisability; and performance will be evaluated at both the cohort and patient-specific levels, assessing whether the models reliably detect meaningful deviations relative to each participant’s baseline over time. Standard classification metrics will be reported for all models using the Ranked Probability Score when applicable. For the 6MWD, CAT, CCQ and mMRC models, a leave-one-subject-out validation strategy will additionally be used with principal component analysis to address collinearity among predictors.

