### Study status

Assessors’ training began in January 2024, totalling approximately 24 hours. Following ethical approval at all participating sites, participant recruitment was conducted from May 2024 to October 2025. As of October 2025, ninety-six participants have been recruited into the study. However, recruitment at Azienda Ospedaliero Universitaria Pisana has been delayed due to pending safety regulatory requirements for research prototype devices.

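### The 6MWT corridor is 20 m at one centre and 30 m at the other two, so cross-centre validation of 6MWD levels can mistake a corridor effect for model error or a difference in exercise capacity

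*Protocol article*

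**What the plan says.** All references are to the protocol article.

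- **Clinical outcomes.** The 6MWT is done at T1, T3 and T5, on a course described as "with a length of 30 m at Azienda Ospedaliero Universitaria Pisana and Hospital del Mar, and 20 m at the Pulmonary Research Institute".
- **Statistical analysis, target.** For 6MWD, CAT, CCQ and mMRC, "we will model their levels and their changes over time, both as continuous and dichotomised according to minimal importance difference", with a cumulative link model or a standard classification model. Levels are thus a stated target.
- **Statistical analysis, validation.** All models use a group-based strategy, "with training and testing sets separated at the clinical centre level to prevent information leakage and assess cross-site generalisability". For 6MWD and the three scores, "a leave-one-subject-out validation strategy will additionally be used with principal component analysis to address collinearity among predictors".
- **Abstract.** The named outcome is "6-month changes in functional exercise capacity through the 6-minute walk test".
- **Statistical analysis, patient level.** Evaluation includes "assessing whether the models reliably detect meaningful deviations relative to each participant’s baseline over time".
- **Strengths and limitations.** Six limitations are listed and corridor length is not among them. The multicentre design is presented as making predictions applicable across the populations studied.

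**The concern.** For the same distance, a participant on a 20 m course covers 50% more lengths than one on a 30 m course and so turns more often. If turning costs time, the recorded distance is shorter for the same exercise capacity. Only the German centre uses 20 m, so corridor length and centre cannot be told apart.

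This matters because of how three fixed choices combine: unequal corridors, levels as a target, and a split by centre. When the 20 m centre is the test set, a level model trained on 30 m data carries no information about the shorter course. When a 30 m centre is the test set, the 20 m data in training pull predictions the other way. In pooled or leave-one-subject-out fits, any sensor or clinical feature that differs by site can stand in for the corridor. At stake is what the cross-site performance of the 6MWD-level models means.

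**Working it through.** The article gives no figure for the corridor effect, so there is none to reproduce. The corridor lengths, target and split come from the article. Seconds per turn, mean, SD, R² and centre sizes below are assumptions.

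**1. Can the data separate corridor from centre?** A design matrix with an intercept, two centre indicators and a corridor indicator has 4 columns and rank 3, so they cannot be separated. With the 20 m centre held out, the corridor indicator has variance 0 in the training data, so no covariate can learn its effect.

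**2. How large might the offset be?** For distance d in 360 s:

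- extra lengths = d/20 − d/30 = d/60
- walking speed = d/360 m/s
- offset = (d/60) × (d/360) × s = d² × s / 21 600, with s = seconds lost per turn

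| d (m) | extra lengths | offset, s = 1 | offset, s = 2 |
|---|---|---|---|
| 300 | 5.0 | 4.2 m | 8.3 m |
| 400 | 6.7 | 7.4 m | 14.8 m |
| 450 | 7.5 | 9.4 m | 18.8 m |

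The range is about 4-19 m.

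**3. What does that do to a level model?** With a constant offset δ at the 20 m centre and equal centres, the expected mean error (observed minus predicted) is −δ when that centre is held out. It is +δ/2 when a 30 m centre is held out, because half the training data then come from 20 m. A simulation of a linear level model (400 runs, 50 participants per centre, mean 400 m, SD 100 m, true R² 0.5) gave:

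| δ (m) | mean error, 20 m centre held out | RMSE | R² | mean error, a 30 m centre held out |
|---|---|---|---|---|
| 0 | 0.0 | 70.5 | 0.48 | −0.4 |
| 10 | −9.6 | 71.6 | 0.46 | +4.9 |
| 20 | −19.4 | 73.5 | 0.43 | +11.0 |

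As a check, the residual variance is 100² × 0.5 = 5000, so RMSE should be near √(5000 + δ²) = 70.7, 71.4 and 73.5 m, which agrees. Offsets of 30 and 50 m bring R² to 0.36 and 0.19, but they lie outside the range in step 2.

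**4. What does it do to change?** A constant offset cancels: (y₂ − δ) − (y₁ − δ) = y₂ − y₁. A proportional effect does not cancel fully. With an assumed mean change of −10 m, a 5-10% effect biases mean change by 0.05 × 10 = 0.5 m to 0.10 × 10 = 1 m. The turn model in step 2 also grows with distance. Its slope is d × s / 10 800, which runs from 300 × 1 / 10 800 = 2.8% to 450 × 2 / 10 800 = 8.3% of any change, or about 0.3-0.8 m on a 10 m change.

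**The case against.** **The named outcome is change, and change is protected.** The abstract names 6-month change, the Introduction speaks of patient-specific models for changes, and patient-level evaluation is against own baseline. Dichotomising at a minimal important difference also fits change most naturally. This stands and limits the point to the level models of a non-primary outcome. Levels are nevertheless a stated target.

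**The effect may be small or absent.** This also stands. A reader might infer that 6MWD is certainly shorter at the German centre and that the artefact will be read as model error. The article gives no corridor effect, and with zero effect the harm vanishes. At 4-19 m, RMSE and R² barely move. Neither is a planned measure: the plan reports classification metrics and the Ranked Probability Score, so step 3 is only illustrative.

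**Held-out centres are meant to differ.** The split is there to assess generalisability, and language, health system and case mix differ too. That is true, but corridor length is a feature of the measuring course, not of patients or care.

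**Leave-one-subject-out validation helps.** It keeps other 20 m participants in training, which lessens the problem. It does not remove it, because site-patterned features can still absorb the corridor effect.

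**This is analysis-plan detail.** A condensed article may leave recalibration to a fuller document, and its silence there is no fault. What it does fix is the combination of corridors, target and split.

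**The Pisa delay.** The Study status section says "recruitment at Azienda Ospedaliero Universitaria Pisana has been delayed due to pending safety regulatory requirements for research prototype devices". A reader might infer that 20 m versus 30 m will be almost the only centre contrast left. No counts by site are given, so this is possible but not shown.

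**Conclusion.** The point holds for the 6MWD-level models only. Corridor length is completely aliased with centre, and that follows from the article without any assumption. Following the plan as written, any corridor effect enters the cross-site performance of level predictions and cannot be separated from centre using the study's own data.

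The size is uncertain. At an assumed 1-2 s per turn the offset is about 4-19 m, which appears mainly as miscalibration at one centre and adds little to overall error. The 6-month change outcome is largely unaffected, provided each participant repeats the test in the same corridor, and exacerbation onset, the primary target, does not use 6MWD as its outcome. A reader might go further and say that cross-site error for raw levels should not be quoted at all. An assumed 4-19 m does not justify that, and showing the raw error beside the recalibrated one is more informative. This is a modest improvement worth making before analysis.

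**What to change.** 1. Make within-participant 6-month change in 6MWD the main 6MWD target for cross-centre validation.
2. For level models, report held-out performance separately by centre, both with and without recalibrating the intercept (or the thresholds of the cumulative link model) in the held-out centre. The gap between the two shows how much of the error is a level shift.
3. State the corridor difference as a limitation on cross-site claims about 6MWD levels.

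This costs a few sentences and no new data. The drawback is that recalibration uses outcome data from the held-out centre and removes true case-mix differences along with any corridor effect. The recalibrated figures are therefore not a pure external test, and claims about predicting absolute 6MWD across sites become narrower. This is why both sets of results should be shown.

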#### Predictors

##### Sensor data

The TOLIFE Kit includes six unobtrusive commercial and research prototypes that will be used continuously during the study (table 1). At each visit, participants are instructed to use all devices according to recommended minimum usage protocols, with the smartphone being mandatory (table 2). However, participants retain the discretion to refrain from using certain devices. The participants can also prospectively indicate periods between visits when they will not be using (some of) the selected devices.

**Table 1 T1:** Embedded sensors and devices and planned raw data to be collected

Sensors	Device	Raw data
Accelerometer	Samsung Galaxy Watch 5, Samsung M13, smartshoes, smart mattress cover	Triaxial acceleration (acceleration in x, y and z axes)
Gyroscope	Samsung Galaxy Watch 5, Samsung M13, smartshoes	Angular velocity (rotation in x, y and z axes)
Photoplethysmography (PPG) sensor	Samsung Galaxy Watch 5, Smart One Oxi	Photoplethysmogram
Microphone	Samsung Galaxy Watch 5, Samsung M13, environmental box	Sound intensity
GPS*	Samsung Galaxy Watch 5, Samsung M13	Latitude and longitude
Light sensor	Samsung Galaxy Watch 5, environmental box	Light intensity
Pressure sensor at 3 points	Smartshoes	Biomechanical pressure
Pressure sensor at 40 points	Smart mattress cover	Biomechanical pressure
Air quality sensor	Environmental box	Air quality, temperature and humidity
Turbine flow sensor	Smart One Oxi	Respiratory airflow

* Although these devices include a GPS sensor, the absolute position of the participant will not be tracked. We will use a derivative parameter that will not allow us to identify the absolute position of the participants.

**Table 2 T2:** Recommended usage time for the TOLIFE Kit

Device	Recommended use
Samsung Galaxy Watch 5	It should be worn at all times and charged overnight.
Samsung M13	It should be kept in a pocket when outside and may rest on any surface at home. It should be charged overnight.
Smartshoes	It should be worn for 60 min/day and charged overnight.
Smart mattress cover	It should remain always activated and used every night for sleep.
Environmental box	It should remain always activated.
Smart One Oxi	Should be used once a week.

Three of them are commercial devices, including the smartwatch Samsung Galaxy Watch 5, the Samsung M13 smartphone and the Smart One OXI spirometer. The smartwatch and smartphone, unlike many other commercial devices, allow direct control of their sensors and provide access to raw data via software development kits, enabling the creation of applications for data collection and sensor management. These devices will gather raw data using their built-in sensors: both the smartwatch and smartphone are equipped with accelerometers, gyroscopes, microphones and GPS. Additionally, the smartwatch contains a photoplethysmography (PPG) sensor and an ambient light sensor. The Smart One OXI spirometer will collect data on pulmonary airflow and uses a PPG sensor. The specific raw data collected by each sensor are detailed in table 1.

The research prototype devices include smart shoes, a smart mattress cover and an environmental unit. The smart shoes are equipped with embedded sensors in the insoles, including accelerometers, gyroscopes and pressure sensors. The smart mattress cover is designed to be placed on top of the participant’s mattress at the thoracic level and collects raw data using accelerometers and pressure sensors.^23^ The environmental unit will be placed in the participant’s bedroom and is equipped with a microphone, ambient light sensor and air quality sensor. As with the commercial devices, the specific raw data collected by these sensors are listed in table 1.

##### Clinical data

We will perform standardised procedures to obtain (1) weight and height from a physical examination at visit T1, from which we will calculate body mass index; (2) total body water, fat mass and fat-free mass from bioelectrical impedance analysis at visits T1 and T5; (3) postbronchodilator FEV_1_ and FVC from forced spirometry^16^ at visits T1, T3 and T5; (4) tidal volume, residual volume, expiratory reserve volume, inspiratory reserve volume, inspiratory capacity, functional residual capacity, vital capacity and total lung capacity from body plethysmography^24^ at visit T1; and (5) diffusing lung capacity for carbon monoxide and alveolar volume from the single-breath carbon monoxide uptake test^25^ at visit T1.

Participants will respond to interviewer-administered validated questionnaires at every visit that will provide data on (1) individual sociodemographic characteristics (only at T1), including employment, marital status, living arrangement, education level, ethnicity; (2) smoking history (status, intensity and duration); (3) sleep quality from the Pittsburgh Sleep Quality Index^26^; (4) anxiety and depression symptoms from the Hospital Anxiety and Depression Scale^27^; and (5) general HRQoL from the 5-level EuroQol 5-Dimension Questionnaire.^28^

Lastly, we will collect data on comorbidities and pharmacological and non-pharmacological treatments from medical records at every visit.

### Statistical analysis

The characteristics of the participants will be summarised using means and SD for continuous variables and frequencies and percentages for categorical variables.

The collected data will be processed through a modular modelling architecture. Low-level models will convert raw sensor outputs from each device (continuous physiological signals, discrete events and questionnaire-derived outcomes) into standardised physiological and behavioural indicators. These indicators, integrated with clinical variables, will serve as inputs to the higher level predictive models.

To predict the onset of moderate-to-severe COPD exacerbations, both rule-based and machine learning approaches will be compared during development, with the single best performing strategy in terms of predictive accuracy and clinical interpretability selected for the final system. The model will output a continuous daily probability score estimating exacerbation risk within a given future time window, rather than a binary prediction. To predict changes in 6MWD, CAT, CCQ and mMRC outcomes, we will model their levels and their changes over time, both as continuous and dichotomised according to minimal importance difference (following the most recent literature cut-offs at the time of data analysis), using a cumulative link model or a standard classification model, respectively. Predictors will consist of sensor-derived indicators, aggregated over different temporal windows (eg, 7, 14, 21 and 30 days for the exacerbation models; 21-day summaries for the 6MWD, CAT, CCQ and mMRC models), together with clinical variables.

For all models, statistical inference will rely on a clustered bootstrap approach with resampling at the participant level to account for repeated measurements; a group-based validation strategy will be adopted, with training and testing sets separated at the clinical centre level to prevent information leakage and assess cross-site generalisability; and performance will be evaluated at both the cohort and patient-specific levels, assessing whether the models reliably detect meaningful deviations relative to each participant’s baseline over time. Standard classification metrics will be reported for all models using the Ranked Probability Score when applicable. For the 6MWD, CAT, CCQ and mMRC models, a leave-one-subject-out validation strategy will additionally be used with principal component analysis to address collinearity among predictors.

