Remote patient monitoring is a promising strategy for proactive COPD care, where sensor-based technologies are central to continuous data collection,^7^ and artificial intelligence (AI) is key to its subsequent integration and analysis. Sensor-based technologies, either worn on the body or placed in the home environment, continuously collect a wide range of physiological and behavioural data to support remote health assessment and potentially enable early detection of clinical deterioration.^8^ The advantages are amplified given that in respiratory disease, passive monitoring strategies (eg, wearable oxygen saturation device) achieve superior patient adherence compared with active methods (eg, manual pulse oximeter recording).^9^ Moreover, AI methods have shown potential to outperform traditional approaches in predicting COPD-related outcomes, particularly when integrating multiple data sources. For example, a random forest classifier outperformed a rule-based symptom detection method in predicting exacerbations within 3 days (area under the receiver operating characteristic curve (AUROC) 0.727 compared with 0.655),^10^ and gradient boosting models have outperformed exacerbation history alone in predicting severe exacerbations (AUROC 0.82 compared with 0.68).^11^ Moreover, combining clinical, environmental and lifestyle data improved 7-day exacerbation prediction (AUROC 0.935 compared with 0.835 when clinical data were excluded).^12^ However, there is still limited evidence on whether sensor-derived data can effectively predict key COPD outcomes or whether constructs increasingly associated with COPD progression, such as gait patterns^13^ and sleep quality,^14^ can effectively improve these predictions.

The TOLIFE Clinical Study A (CSA) aims to train, internally validate and test a modular AI-based analytical framework that integrates clinical data from standardised tests with continuously gathered daily-life data from six unobtrusive devices (smartphone, smartwatch, portable spirometer, smartshoes, smart mattress cover and environmental box). The primary prediction target is the timing of onset of moderate-to-severe exacerbations. Separate patient-specific models will address changes in HRQoL, dyspnoea severity and functional exercise capacity.

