## Discussion

COPD management is increasingly moving towards precision medicine. Initially, the GOLD guidelines relied solely on an FEV_1_-focused approach to guide treatment.^29^ Over time, this shifted to a patient-centred model, prioritising patients’ symptoms and exacerbation history.^30^ More recently, the guidelines have evolved to support personalised follow-up and introduce treatment strategies based on Treatable Traits.^31^ Still, challenges remain. Exacerbation history is the strongest predictor of future exacerbations,^32^ but COPD heterogeneity poses particular challenges, as patients with similar clinical profiles and exacerbation histories face different disease progression.^33^ Smart sensing technologies appear as promising complementary tools. These devices provide continuous, real-time monitoring of physiological parameters that can capture the clinical variability of COPD, allowing for personalised prediction estimates of exacerbations and early detection of changes in HRQoL, dyspnoea severity and exercise capacity.

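### The described analysis plans no model without sensors and no last-visit reference, and does not name exacerbation history as a predictor, so as planned it would not show what the sensors add

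*Protocol article*

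**What the plan says.** The Introduction gives as motivation that "there is still limited evidence on whether sensor-derived data can effectively predict key COPD outcomes", and asks in the same sentence whether constructs such as gait and sleep quality improve such predictions.

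The Statistical analysis section then fixes the inputs. Of the sensor indicators it says: "These indicators, integrated with clinical variables, will serve as inputs to the higher level predictive models". It repeats the point for all outcomes: "Predictors will consist of sensor-derived indicators, aggregated over different temporal windows", with clinical variables alongside. For exacerbations, "both rule-based and machine learning approaches will be compared during development, with the single best performing strategy" is to be chosen "in terms of predictive accuracy and clinical interpretability selected for the final system". For CAT, CCQ, mMRC and 6MWD, both levels and changes are modelled. Inference uses a bootstrap that resamples participants, and performance is assessed at cohort and patient-specific level.

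The Discussion states: "Exacerbation history is the strongest predictor of future exacerbations". The Clinical data section, under Predictors, lists lung function, body composition, questionnaires and smoking history, and ends with the record-based items: "we will collect data on comorbidities and pharmacological and non-pharmacological treatments from medical records at every visit". Exacerbation history is not named there. It appears in the Participants section as an entry criterion, and exacerbations during the study appear in the Clinical outcomes section.

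**The concern.** Whether a data source improves prediction is a comparative question: it needs the same model with and without that source. The one comparison described varies the algorithm while the inputs stay the same mix. A good cohort-level result for the combined model could reflect the sensors, the clinical variables or both, and nothing in the plan separates them.

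Two features make this more pressing. First, a person's previous score is informative about the next one, so a model of CAT, CCQ, mMRC or 6MWD levels can look good with no sensor signal at all unless it is set against the last visit. Second, if exacerbation history is not among the candidates, sensor indicators might pick up part of what history would have told the clinician. That is a plausible risk, not a demonstrated one.

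At stake is the main inference readers will want to draw: whether a six-device kit is worth wearing for a year beyond what the clinic already knows.

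**Working it through.** **1. The plan's own figures.** Participants section: 150 participants and 0.71 exacerbations per person-year. 150 × 0.71 = 106.5, which matches the stated 106. 150 × 360 = 54,000 daily observations, which also matches. The article gives no power figure to reproduce.

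**2. Question against analysis.**

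| Needed to answer the Introduction's question | Described in the article? |
|---|---|
| Model with sensors and clinical variables | Yes, for every outcome |
| Same model without sensors | No |
| Last-visit reference for score levels | No |
| Exacerbation history named as a predictor | No |
| Performance difference between input sets | No |
| Data for all of the above | Yes: Participants, Clinical outcomes, Clinical data |

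The gap is therefore in the described analysis and not in the data collection.

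**3. How much a last-visit reference could explain.** The documents give no visit-to-visit correlation r, so r = 0.7 to 0.8 is an assumption. With equal means and variances at both visits, carrying the last score forward has error variance 2σ²(1 − r). The share of variance explained is 1 − 2(1 − r) = 2r − 1:

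- r = 0.7: 2 × 0.7 − 1 = 0.40
- r = 0.8: 2 × 0.8 − 1 = 0.60

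This is 40% to 60% without any sensor. The square of r (0.49 to 0.64) belongs to a regression fitted on the last score, not to carrying it forward. These figures illustrate why a reference is needed for levels. They do not measure the problem in this cohort, and they do not apply to the change outcomes.

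**4. How precisely the difference could be estimated.** Study status reports 96 recruited by October 2025. 96 × 0.71 = 68.2, about 68 events if each contributes a full year. Under the article's rule of 10 events per candidate predictor, 106/10 = 10.6 and 68/10 = 6.8, so about 10 and 6 to 7 predictors.

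For illustration only, assume a participant-level outcome of at least one event, with Poisson probability 1 − exp(−0.71) = 0.51 (76 of 150, or 49 of 96), Hanley–McNeil standard errors, a correlation of 0.3 to 0.7 between the two AUROCs, and placeholder AUROCs of 0.68 without and 0.75 with sensors:

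| Participants | SE of difference | 95% half-width (1.96 × SE) | Power for 0.68 to 0.75 |
|---|---|---|---|
| 150 | 0.032 to 0.049 | 0.06 to 0.10 | 29% to 58% |
| 96 | 0.041 to 0.062 | 0.08 to 0.12 | 20% to 41% |

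A gain of 0.14 (0.68 to 0.82) would be shown with 85% to 99% power at 150 and 67% to 95% at 96. Only a large gain would be shown firmly. The real target is a daily probability, so these are orders of magnitude.

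**The case against.** The strongest reply is that incremental value is not a stated objective. The aim is to train, internally validate and test an integrated framework, the Introduction's question is background, and benchmark models are often left to a full protocol or SAP that is not shown. It stands that no promise is broken. But the article does state its predictors and its comparison, and what it states does not meet the gap it cites as its reason. Planned variable selection does not fill that gap either: it shows which variables survive, not how much performance they bring.

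Several stronger readings are tempting and are not supported:

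- *The study cannot show whether sensors help.* A reader might infer this, but prior-year history, dated exacerbations, scores, 6MWD, FEV1, comorbidities and treatments are all collected. The benchmark is not planned; it is not prevented.
- *Exacerbation history is left out of the models.* The Clinical data list is not shown to be closed (it does not name age either), and the Statistical analysis section says only clinical variables. Entry requires at least one prior event, so history varies only in number and severity, which limits what it can contribute.
- *All performance could come from clinical variables.* That is possible for pooled metrics. The patient-specific evaluation, relative to each person's own baseline, partly isolates sensor signal, because variables fixed at T1 cannot produce within-person detection and the others update only at visits. No reference is named at that level either.
- *The AUROCs cited in the Introduction give the size.* The pair 0.935 and 0.835 concerns 7-day exacerbation prediction with and without clinical data. The pair 0.82 and 0.68 concerns severe exacerbations against history alone. They come from different studies and outcomes, and neither measures what this kit adds.

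**Conclusion.** The point holds in limited form. As described, the plan has no benchmark without sensors and no last-visit reference for score levels, and does not name exacerbation history as a predictor. Followed as written, it would leave cohort-level performance unattributable to the sensors and the Introduction's question unanswered.

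The documents do not allow the effect on the results to be sized. The 40% to 60% for carrying a score forward rests on an assumed correlation and concerns levels only. The conclusion depends on the article's description being the operative plan; a fuller document that already specifies the comparison would settle it. It is a worthwhile change to make before analysis, and not a flaw that invalidates the study.

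**What to change.** Before analysis, prespecify for each outcome, on identical folds:

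- a clinical-only benchmark that includes the prior-year exacerbation count documented at eligibility and, for CAT, CCQ, mMRC and 6MWD, the last-visit value;
- the same model plus the sensor indicators;
- for levels, a no-change reference that carries the last score forward.

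Report the paired difference in discrimination, in calibration or log loss, and in net benefit (which the article already invokes for its high-sensitivity use), with the participant-level bootstrap interval already planned, at cohort and patient-specific level. Name exacerbation history in the list of clinical predictors.

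No new visits or procedures are needed, and the history variable is already checked at screening. The cost is additional model fits, repeated across outcomes, levels and changes, continuous and dichotomised forms, and validation schemes. The benchmark also uses part of a small predictor allowance (about 10 at 106 events, 6 to 7 at 68), so its variables should be few and fixed in advance. With so few events the difference will be imprecise. Present it as an estimate with its interval, and do not read an interval that includes zero as proof that the sensors add nothing.
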